## Secondary Efficacy Analyses

### 90-day mRS 0-2

The proportion of 90-day mRS 0-2 will be analyzed using a binary logistic regression model with site as a random effect. The odds ratio with 95% CI will be reported.

### 90-day mRS 0-3

The proportion of 90-day mRS 0-3 will be analyzed using a binary logistic regression model with site as a random effect. The odds ratio with 95% CI will be reported.

### 36h (24-48h) NIHSS 0-1 or decrease $\geq 10$ from baseline

The proportion of 36h (24-48h) NIHSS 0-1 or decrease  $\geq 10$  points from baseline will be analyzed using a binary logistic regression model with site as a random effect. The

---

odds ratio with 95% CI will be reported.

### **36h (24-48h) infarct volume change (by CT or MRI)**

The change of 36h (24-48h) infarct volume change (by CT or MRI) will be analyzed using student t-test or Wilcoxon rank sum test as appropriate.

### **36h (24-48h) target artery recanalization rate (by CTA or MRA)**

The 36h (24-48h) target artery recanalization rate (by CTA or MRA) will be analyzed using a logistic regression model with site as a random effect. The odds ratio with 95% CI will be reported.

## **13.Safety Analyses**

All analyses of safety data will be carried out using the safety set (SS) population.

### **Primary Safety Endpoints**

Rate of symptomatic intracranial hemorrhage within 48 hours from randomization (Heidelberg Bleeding Classification).

### **Secondary Safety Endpoints**

All-cause mortality within 90 days.

Rate of any intracranial hemorrhage within 48 hours from randomization (Heidelberg Bleeding Classification).

Rate of decompressive hemicraniectomy during hospitalization.

For most bleeding events, the binary logistic model with site as a random effect will be used to compare the odds ratio between the two treatments, or Poisson regression or negative binomial regression which are more appropriate for the analysis of rare event. For all-cause mortality within 90 days, the Cox proportional hazards model with site as a random effect will be used to compare the hazard ratio between the two treatments.

### **Adverse Events**

Adverse events (AEs) will be coded using the MedDRA coding dictionary (Version 6.0 or a later release) and grouped by system organ class (as detailed in the study protocol).

---

Separate data display listings and summaries will be presented for adverse events that start prior to first dose of study medication (pre-treatment), whilst on study medication (during treatment) and after the last dose of study medication (post-treatment).

Within each treatment group, the number and percentage of subjects experiencing an AE will be summarized by system organ class and preferred term and Fisher's Exact test will be used to compare the number of each grouped AE event between treatment groups. In addition, a separate summary will be provided for AEs experienced by more than 5% of subjects in either of the treatment groups.

### **Serious Adverse Events**

Summary tables and data displays will be provided for serious adverse events (as detailed in the study protocol). In addition, all deaths and serious AE's will be documented in a case narrative format in the clinical study report.

The number of adverse events or serious adverse events occurring over the treatment period will be summarized and Fisher's Exact test will be used to compare between treatment groups.

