### **(3) Safety Analysis**

Safety events in the two treatment groups will be described based on the SAS dataset. Logistic regression will be used to compare the differences in safety endpoints such as intracranial bleeding events between the two groups. Chi-square test and Fisher's exact test will be used to compare the differences in the incidence of AEs and SAEs between the two groups.

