### Event Rates

The number of events should be recorded in detail and showing the event rate in 90 days of each treatment group in summary statement.

The event rate for each treatment group will be calculated as: the sum of number of event for all the patients / the sum of number of treatment periods for all the patients.

---

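### SAP v2.0 words the Fisher's exact tests of AEs and SAEs on numbers of events rather than patients with an event, and leaves the analysis window undefined

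*Supplement*

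**What the plan says.** SAP v2.0, section 13, Serious Adverse Events: "The number of adverse events or serious adverse events occurring over the treatment period will be summarized". On that number, the plan sets the arms against each other with a Fisher's exact test.

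SAP v2.0, section 13, Adverse Events: "the number and percentage of subjects experiencing an AE will be summarized by system organ class and preferred term", and in the same sentence "Fisher's Exact test will be used to compare the number of each grouped AE event between treatment groups". The summary is therefore of patients and the test clause is of events. The same section splits AE listings and summaries into phases, namely "adverse events that start prior to first dose of study medication (pre-treatment), whilst on study medication", and a third phase after the last dose.

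SAP v2.0, section 10, Event Rates, mentions a 90-day rate but divides the total number of events by "the sum of number of treatment periods for all the patients". The SAP does not define the treatment period.

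Protocol V7.1, 10.3.2 (3): "Chi-square test and Fisher's exact test will be used to compare the differences in the incidence of AEs and SAEs between the two groups". Protocol 9.2.1 and 9.3 set AE collection from consent or randomization to the last planned or closure visit, with no distinction by arm.

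**The concern.** Fisher's exact test compares two proportions of independent units. A patient who has three SAEs adds three to an event total, and those three are not independent. The test then underestimates the variability of the difference. Event totals also have no natural complement for a 2x2 table, because the number of events can exceed the number of patients. The protocol's word, incidence, points to patients with an event. As the SAP stands, two programmers could follow the two documents and obtain different p-values from the same data.

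The window adds a second ambiguity. What is randomized is a procedure added to medical management, so there is no study medication with a first and a last dose. The treatment period could be read as the procedure, the hospital stay or the whole follow-up, and in an open-label trial that choice should not be left until data exist.

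**Working it through.** **Inputs from the documents.** 251 per arm (SAP v2.0, section 6); two-sided tests at 0.05 for general analyses (SAP v2.0, section 9). The plan gives no AE rate and no number of events per patient, so both are assumptions below.

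**The plan's own figure.** The plan has no figure for the AE comparison; its sample size supplies only the number per arm. It can be reproduced from the proportional-odds formula N = 12(z_a + z_b)² / [ln(OR)² (1 − Σp̄³)]. With two-sided alpha 0.046, power 0.90, OR 1.73 and the stated control mRS distribution, (1.995 + 1.282)² = 10.738, ln(1.73)² = 0.3004 and Σp̄³ = 0.0475. This gives N = 450.3 against the stated 452, and 452/0.9 = 502.2 against 502.

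**Type I error.** The simulation assumes no true difference, 3,000 replicates per scenario and Fisher's test at 0.05. A share p of patients (0.05, 0.1, 0.2, 0.3 or 0.5) has at least one event. Each affected patient has 1 + G events, where G is negative binomial with mean m and size 1. The SAP names no table for event totals, so two were tried. Ranges are over the five values of p.

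| Mean events per affected patient (1 + m) | Patients with an event | Events vs N minus events | Events vs patients without an event |
|---|---|---|---|
| 1 | 0.029–0.048 | 0.029–0.048 | 0.029–0.048 |
| 1.25 | 0.035–0.042 | 0.09–0.18 | 0.07–0.09 |
| 1.5 | 0.029–0.043 | 0.13–0.34 | 0.09–0.13 |
| 2 | 0.028–0.049 | 0.24–0.54 | 0.13–0.22 |

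The top value, 0.54, is at p = 0.5 and mean 2. There the events vs N minus events table could not be formed in 73% of replicates, because events exceeded patients, and 0.54 refers to the rest. Among scenarios in the table where it could always be formed, the highest value is 0.39 (p = 0.3, mean 2). At p = 0.5 and mean 3 the table could never be formed.

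**Hand check of one cell** (p = 0.2, mean 1.5, so m = 0.5). E[X²] for an affected patient is m + m² + (1 + m)² = 0.75 + 2.25 = 3.0. The true variance per patient is 0.2 × 3.0 − (0.2 × 1.5)² = 0.60 − 0.09 = 0.51. The test assumes 0.3 × 0.7 = 0.21. The ratio is 2.43 and its square root 1.56, so the real level is about 2Φ(−1.96/1.56) = 0.21. The simulation gave 0.19.

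**Window, as an illustration only.** Assume equal hazards of 0.2 events per patient per 90 days, so the proportion affected by day d is 1 − exp(−0.2d/90). If one arm were counted to day 30 and the other to day 90, these would be 6.4% and 18.1%. The normal-approximation power formula for two proportions puts the chance of declaring a difference at about 98%. For 75 against 90 days (15.4% and 18.1%) it is about 13%. The SAP does not prescribe unequal windows. The figures show only why the window has to be stated.

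**The case against.** The strongest reply is that a patient-level test was intended. The Adverse Events sentence opens with numbers and percentages of subjects, the next sentence uses a threshold of 5% of subjects, the protocol says incidence, and section 1 of the SAP asks to be read with the protocol. Fisher's test also needs a 2x2 table, and patients supply the only workable one. This stands as a reason to call the fault one of wording. It does not remove it: both test clauses and the event-rate formula count events, and the SAP is the document meant to settle the unit.

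Three stronger readings are tempting and are not supported.

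- *The tests are tied to dose dates.* The Serious Adverse Events section mentions no doses, and the dose-based phases govern only listings and summaries.
- *The arms have no common window.* The protocol collects AEs over the same period in both arms, and Event Rates mentions 90 days. What is missing is a stated analysis window for the AE/SAE tests.
- *The p-values will be too small.* That holds only if some patients contribute more than one event. With at most one each, Fisher's test stays at or below its nominal level.

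The consequence is also limited. Symptomatic and any intracranial hemorrhage, mortality and hemicraniectomy are separately defined endpoints, with models given for bleeding and mortality. The documents attach no decision rule to the AE/SAE tests.

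**Conclusion.** The point holds for the unit of analysis and for the undefined window. Followed literally, the AE and SAE tests treat repeat events in one patient as independent, or have no valid table. Under no true difference with 251 per arm, the type I error is about 0.07 to 0.54 if affected patients have a mean of 1.25 to 2 events, depending on the table used and the share of patients affected. It is about 0.03 to 0.05 if each patient is counted once or has at most one event. The recurrence rates and event shares are assumptions, so these figures are a range of what could happen and not a forecast. The treatment period is undefined both in the SAE comparison and in the rate denominator, and the study-medication phases do not suit this trial. The SAP should be corrected, but the matter concerns supportive safety comparisons only; neither the primary endpoint nor the named safety endpoints are touched.

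**What to change.** In SAP section 13:

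- Apply Fisher's test to the number of safety-set patients with at least one event, overall, by system organ class, and for SAEs. This agrees with the protocol's incidence.
- State one window from randomization, the same in both arms, for example to day 90 and separately to 12 months.
- Report event totals descriptively, or with a count model using person-time.
- Replace the study-medication phases with time from randomization.

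In SAP section 10, define the event rate as safety-set patients with the event divided by all safety-set patients in the arm. The safety set (treated, with at least one safety evaluation) is not the same as all randomized patients, so the denominator should be named as the safety set.

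The cost is SAP wording and the matching table shells. No new data and no protocol amendment are needed.

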## Revisions to previous SAP version

| SAP version 1.0                                                                                                                                                                                                                                                                                                                                                                                                                                                                                                                                                                                                                                                                                                                                                                                                                                                                                                                                                                                                                      | Changes in SAP version 2.0                                                                                                                                                                                                                                                                                                                                                                                                                                                                                                                                                                                                                                                                                                                                                                                                                                                                                                                                                                                                        |
|--------------------------------------------------------------------------------------------------------------------------------------------------------------------------------------------------------------------------------------------------------------------------------------------------------------------------------------------------------------------------------------------------------------------------------------------------------------------------------------------------------------------------------------------------------------------------------------------------------------------------------------------------------------------------------------------------------------------------------------------------------------------------------------------------------------------------------------------------------------------------------------------------------------------------------------------------------------------------------------------------------------------------------------|-----------------------------------------------------------------------------------------------------------------------------------------------------------------------------------------------------------------------------------------------------------------------------------------------------------------------------------------------------------------------------------------------------------------------------------------------------------------------------------------------------------------------------------------------------------------------------------------------------------------------------------------------------------------------------------------------------------------------------------------------------------------------------------------------------------------------------------------------------------------------------------------------------------------------------------------------------------------------------------------------------------------------------------|
| 
5. Design
 
The planned sample size is 488 cases, and two analyses will be conducted when the 90-day follow-up of 1/2 (244 cases) and 3/4 (366 cases) of the total sample size is completed.
                                                                                                                                                                                                                                                                                                                                                                                                                                                                                                                                                                                                                                                                                                                                                                                                                             | 
5. Design
 
The planned sample size is 502 cases, and two analyses will be conducted when the 90-day follow-up of 1/3 (168 cases) and 2/3 (336 cases) of the total sample size is completed.
                                                                                                                                                                                                                                                                                                                                                                                                                                                                                                                                                                                                                                                                                                                                                                                                                          |
| 
6. Sample size estimates
 
...The average treatment effect of EVT improved the outcome with the common OR value for improvement of mRS reached 1.74; (3) Two Interim analysis were considered. Adjusted level <math>\alpha=0.05</math> and power <math>1-\beta=0.90</math>. (4) The sample size was allocated to the intervention group and the control group in a 1:1 ratio. Based on these parameters, the total sample size was 438. Considering 10% attrition rate, the final total sample size was 488 cases, 244 cases in each group.
 
Interim analysis will take place when 1/2 (244 cases) and 3/4 (366 cases) have completed 3-month follow-up. O'Brien-Fleming boundaries will be used at the interim analysis as follows:
 
... For an RCT comparing two treatment groups with respect to a binary outcome and two interim analysis, corresponding significance levels based on O'Brien & Fleming boundary are two-sided 0.003 (stage 1), 0.018 (stage 2) and 0.044 (stage 3, final analysis).
 | 
6. Sample size estimates
 
...The average treatment effect of EVT improved the outcome with the common OR value for improvement of mRS reached 1.73; (3) Two Interim analysis were considered. Adjusted level <math>\alpha=0.046</math> (two-sided) and power <math>1-\beta=0.90</math>. (4) The sample size was allocated to the intervention group and the control group in a 1:1 ratio. Based on these parameters, the total sample size was 452. Considering 10% attrition rate, the final total sample size was 502 cases, 251 cases in each group.
 
Interim analysis will take place when 1/3 (18 cases) and 2/3 (336 cases) have completed 3-month follow-up. O'Brien-Fleming boundaries will be used at the interim analysis as follows:
 
... For an RCT comparing two treatment groups with respect to a binary outcome and two interim analysis, corresponding significance levels based on O'Brien & Fleming boundary are two-sided 0.0002 (stage 1), 0.0123 (stage 2) and 0.046 (stage 3,
 |

|                                                                                                                                                                                                                                                                                                                                                                                                                                                                                                                                                                    |                                                                                                                                                                                                                                                                                                                                                                                                                                                                                                                                                                                                                                                            |
|--------------------------------------------------------------------------------------------------------------------------------------------------------------------------------------------------------------------------------------------------------------------------------------------------------------------------------------------------------------------------------------------------------------------------------------------------------------------------------------------------------------------------------------------------------------------|------------------------------------------------------------------------------------------------------------------------------------------------------------------------------------------------------------------------------------------------------------------------------------------------------------------------------------------------------------------------------------------------------------------------------------------------------------------------------------------------------------------------------------------------------------------------------------------------------------------------------------------------------------|
|                                                                                                                                                                                                                                                                                                                                                                                                                                                                                                                                                                    | final analysis).                                                                                                                                                                                                                                                                                                                                                                                                                                                                                                                                                                                                                                           |
| 
The predefined subgroups including:
 
 
• Age (< 75 vs. ≥75)
 
• Last known well to randomization time (< 6h vs. ≥ 6h)
 
• Stroke severity before randomization (NIHSS<16 vs. NIHSS≥16)
 
• Intravenous thrombolysis or not
 
• Occlusion site (ICA vs. M1 segment)
 
• ASPECT score (< 3 points vs. ≥3 points)
 
• Infarct core volume (< 70ml vs. ≥70ml)
 
• Etiological stroke subtype (cardiac embolism vs. large artery atherosclerosis)
 
 | 
The predefined subgroups including:
 
 
• Age (< 75 vs. ≥75)
 
• Weak-up stroke or not
 
• Last known well to randomization time (< 6h vs. ≥ 6h)
 
• Stroke severity before randomization (NIHSS<16 vs. NIHSS≥16)
 
• Intravenous thrombolysis or not
 
• Occlusion site (ICA vs. M1 segment)
 
• Ipsilateral carotid artery occlusion or not
 
• ASPECT score (< 3 points vs. ≥3 points)
 
• Infarct core volume (< 70ml vs. ≥70ml)
 
• Etiological stroke subtype (cardiac embolism vs. large artery atherosclerosis)
 
 |

